### Monitoring and follow-up

All source data are located in worksheets and medical records. A study nurse on each site will register data in REDCap and members of the steering committee will monitor data regularly. All patients will be followed up according to Swedish national guidelines after breast cancer treatment with annual mammography up to 10 years and physical examination after 1 year. At the 1-year follow-up patients will answer the postoperative version of the Breast-Q™ questionnaire, which will be administered either by post or at the one-year check-up appointment. After 5 years, the patient’s medical records will be reviewed to evaluate the number of local recurrences or a new primary cancer ipsi- or contralaterally. See Fig. 1 for study flow chart.

**Fig. 1 Fig1:**
[figure not shown]
Study flow chart

### Statistical methods

#### Power calculation

Based on the assumption that treatment planning will be modified in 18% of patients undergoing CEM, 195 patients will be needed in each arm to show that this proportion is significantly larger than a null proportion of 10%, using a power of 90% and an alpha value (two-sided) of 5%. We will recruit 220 patients per arm (440 patients in total) to account for a drop-out rate of approximately 10%.

The power calculation for the number of participants in this study is based partly on the result of the feasibility study, in which changes were made in the treatment plan in 10 out of 47 cases (21%) after CEM [21]. In previous studies, CEM and MRI have shown similar sensitivity and specificity in breast imaging. The results of the present study will thus also be compared with those of the POMB study in which preoperative MRI was used [13] resulting in changes in the treatment plan in 18% of cases.

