### Study design

This is a prospective randomized multicenter trial. The primary endpoint could have been addressed in a prospective cohort study, but most secondary endpoints need a control group to be answered, explaining the chosen study design. A prospective randomized trial also reduces the risk of selection bias.

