### Patient enrollment

Potential participants in this prospective multicenter trial will be identified at preoperative multidisciplinary team (MDT) conferences after diagnostic work-up of suspicious breast cancer detected by mammographic screening or clinical symptoms. The study will include 440 patients with strongly suspected or an established diagnosis of primary breast malignancy, for whom surgery is planned to involve either partial or total mastectomy based on mammography, ultrasound and core biopsy or cytological examinations. The participants will be randomized either to additional imaging with CEM or to no further preoperative imaging. The findings of CEM will be considered at a second MDT conference, at which changes may be made to the primary treatment plan. The inclusion and exclusion criteria are given in Table 1.

**Table 1 Tab1:** Inclusion and exclusion criteria

**Inclusion criteria**	Planned primary surgery for suspected or verified primary breast malignancy
	Age ≥ 18 years
	Signed informed consent
**Exclusion criteria**	Planned neoadjuvant therapy
	On-going pregnancy
	Iodinated contrast agent allergy
	Renal disease or abnormal S-creatinin (normal range 45–90 μmol/l)
	Untreated thyrotoxicosis (including multinodular goitre) (upon suspicion check P-thyrotropin level, exclusion if < 0.4 mIE/l)
	Severe heart failure
	Myastenia gravis
	Breast implant
	Local recurrence as index lesion
	Inability to understand oral or written information about the study

Study inclusion started in November 2020 and inclusion of the required number of participants is expected to take between two and 3 years depending on the ongoing pandemic of Covid-19. Patients diagnosed at the breast centers in Helsingborg, Kristianstad and Halmstad in Sweden, will be included.

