#### Statistical analyses

Descriptive statistics for parametric variables will be expressed as the median, interquartile range and range. Descriptive statistics for non-parametric variables will be presented as frequencies and percentages. Fisher’s exact test will be used to identify differences between groups and subgroups when applicable.

Pearson’s correlation coefficient and Bland–Altman statistics will be used for each modality regarding preoperative size estimation of the malignant changes compared with histopathological examination. Mean and median values of the largest individual lesion and the total extent will be presented. A separate analysis will be carried out for an extent maximum of 5 cm due to the limitations in assessment by US due to the size of the probe.

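### The figure of 195 is a one-sample size for the CEM arm, not a requirement for each arm, and the only named hypothesis test does not test the hypothesis it was sized for

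*Protocol article*

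**What the plan says.** The Power calculation section starts from a change rate in one group only: "Based on the assumption that treatment planning will be modified in 18% of patients undergoing CEM". The comparison is with a fixed proportion, yet the result is given as a two-arm requirement: "195 patients will be needed in each arm to show that this proportion is significantly larger than a null proportion of 10" per cent, "using a power of 90% and an alpha value (two-sided) of 5" per cent. It is raised to 220 per arm, 440 in total, for about 10% drop-out. No rate is assumed for arm B.

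Under Statistical analyses the only hypothesis test is Fisher's: "exact test will be used to identify differences between groups and subgroups when applicable". Everything else there is descriptive or concerns agreement in tumor size (Pearson correlation, Bland–Altman). No comparison of the CEM arm with 10% appears.

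Two other sections bear on the role of arm B. Study design says "The primary endpoint could have been addressed in a prospective cohort study" and explains that the control group is there for most of the secondary endpoints. Patient enrollment says "The findings of CEM will be considered at a second MDT conference"; no corresponding second decision point is described for arm B.

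**The concern.** The sample-size hypothesis and the stated requirement do not fit together. A comparison with a fixed proportion involves one group, so it cannot generate a number needed in both. Someone who reads the each-arm wording alongside 1:1 randomization and a between-group test may conclude that the primary analysis compares the arms with 90% power. No such comparison was powered.

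The choice of test also matters for the result. The one-sample test asks whether CEM changes the plan in more than 10% of patients. Fisher's test asks whether the arms differ. The primary endpoint is change brought about by CEM findings, and arm B has no CEM, so its rate may be close to zero by construction. A between-arm difference would then be a much lower bar than the 10% the authors chose.

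**Working it through.** **Inputs** (all from Power calculation): p1 = 0.18, p0 = 0.10, two-sided alpha 5% (z = 1.960), power 90% (z = 1.282), stated n = 195, recruited 220 per arm.

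**1. Reproduce 195 as a one-sample size.**

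n = [(1.960·√(0.10·0.90) + 1.282·√(0.18·0.82)) / 0.08]² = [(0.588 + 0.492) / 0.08]² = 182.4

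Continuity correction: (n/4)·[1 + √(1 + 2/(n·0.08))]² = 45.59 × (1 + 1.0663)² = 194.7, rounded up to **195**.

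The stated figure is matched. Drop-out is consistent too: 195/0.9 = 217, and 220 × 0.9 = 198 evaluable.

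**2. Check that a two-sample formula does not give 195.** For 18% vs 10%, two-sided 5%, 90% power:

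n per arm = [1.960·√(2·0.14·0.86) + 1.282·√(0.18·0.82 + 0.10·0.90)]² / 0.08² = 393.3, so 394 (418 with continuity correction).

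Relaxing it does not reach 195 either: 295 per arm at 80% power two-sided, 321 at 90% power one-sided.

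**3. Exact one-sample test of the CEM arm against 10%** (upper tail at most 0.025).

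| n | Changes needed | Upper tail at 10% | Power at 18% |
|---|---|---|---|
| 195 | 29 (14.9%) | 0.020 | 89.3% |
| 198 | 29 (14.6%) | 0.024 | 91.0% |
| 220 | 32 (14.5%) | 0.020 | 92.6% |

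At n = 195, 28 changes fail (upper tail 0.033).

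**4. Fisher's test at 195 per arm, if it were applied to the primary endpoint.** The arm B count is not given in the document, so a range is shown.

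| Changes in arm B | Smallest significant count in CEM arm | p |
|---|---|---|
| 0 | 6 (3.1%) | 0.030 |
| 2 | 10 (5.1%) | 0.036 |
| 4 | 13 (6.7%) | 0.044 |
| 10 | 22 (11.3%) | 0.041 |

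With no changes in arm B, 5/195 gives p = 0.061, so 6 is the threshold. In that case any count from 6 to 28 would be significant by Fisher's test and would not exceed 10% by the one-sample test.

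**5. Fisher power at 195 per arm, with 18% in the CEM arm and an assumed arm B rate:** 57% at 10%, 81% at 8%, 89% at 7%, 98% at 5%, practically 100% at 2% or less. At 220 per arm and an arm B rate of 10% it is 64%. The normal approximation at an arm B rate of 10% gives 63% (195 per arm) and 68% (220 per arm).

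**The case against.** The strongest reply is that nothing is miscalculated and the design is largely explained. The sample-size sentence speaks of a null proportion among patients who undergo CEM, which is one-sample language. Study design concedes that a cohort could answer the primary question. With 1:1 allocation arm B is simply the same size. A careful reader can reach the right interpretation. All of that stands, and it limits the point to wording and consistency. It does not make the each-arm statement correct.

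A second reply is that the qualifier on Fisher's test (used where applicable) does not assign it to the primary endpoint. Fisher's test suits reoperation, avoidable mastectomy and the subgroup questions, and a separate analysis plan may name the one-sample test. This also stands: the document does not say that Fisher's test will decide the primary endpoint. But then no test named in the article addresses the hypothesis that fixed the sample size, and a separate plan would not correct the each-arm sentence.

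A reader might also infer that the trial needs about 394 patients per arm and has only 57–68% power. The document does not support that. Those figures require a 10% change rate in arm B, whereas 10% is stated only as a fixed null for the CEM arm. Nor can one say that no between-arm comparison reaches 90% power: 18% vs 5% has 98%.

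**Conclusion.** The text is wrong as written on one point and inconsistent on another. The figure of 195 belongs to the CEM arm alone, and the one named hypothesis test does not correspond to the powered hypothesis. The primary sample size itself is adequate for the one-sample question: exact power is marginally below 90% at 195 and above it at the 198 expected after drop-out, given the authors' 18% and 10%.

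The practical size of the mismatch depends on the arm B rate, which is not stated. At its widest, with no changes in arm B, the threshold for a positive result is 3.1% under one test and 14.9% under the other. The gap narrows as arm B changes increase. This merits a clarifying correction before analysis; it is not grounds for enlarging the trial.

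**What to change.** In Power calculation, state that 195 evaluable patients are needed in the CEM arm for a one-sample test of 18% against 10%; that arm B has the same size because of 1:1 allocation and serves the secondary endpoints; and that the 90% power does not extend to comparisons between arms.

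In Statistical analyses, name the one-sample test of the CEM arm against 10% as the primary analysis, for example an exact binomial test with a 95% confidence interval. Keep Fisher's test for between-arm secondary endpoints and subgroup comparisons.

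This changes wording only. Recruitment, allocation and the power for the primary question stay as they are. The price is that the article can claim no 90% power for reoperation, avoidable mastectomy or any other between-arm endpoint unless that is calculated separately from stated rates.

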#### Statistical analyses

Descriptive statistics for parametric variables will be expressed as the median, interquartile range and range. Descriptive statistics for non-parametric variables will be presented as frequencies and percentages. Fisher’s exact test will be used to identify differences between groups and subgroups when applicable.

Pearson’s correlation coefficient and Bland–Altman statistics will be used for each modality regarding preoperative size estimation of the malignant changes compared with histopathological examination. Mean and median values of the largest individual lesion and the total extent will be presented. A separate analysis will be carried out for an extent maximum of 5 cm due to the limitations in assessment by US due to the size of the probe.

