#### Secondary endpoints

Do preoperative CEM findings affect the frequency of reoperation or the number of pathologically avoidable mastectomies?Does preoperative CEM show better accuracy in tumor size estimation than mammography and ultrasound, in comparison with histopathological examination?Do other factors such as age, postmenopausality, breast density, type of cancer, or the presence of micro calcifications influence the added value of CEM regarding changes in the treatment plan and tumor size estimation?Is there a difference in health-related quality of life between patients that have undergone preoperative CEM and those who have not?What are the costs and benefits of additional CEM in a health-economic perspective?Does preoperative CEM affect the number of loco regional recurrences/ipsilateral new cancers or contralateral cancer within 5 years?

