### Pre- and postoperative assessment and data collection

At study inclusion, a primary treatment plan must have been decided upon, based on information obtained from findings at mammography, ultrasound, and core biopsy/cytology, according to current clinical standards. (Additional file 3). This plan may be subject to change after the clinical examination at the appointment when the diagnosis is given to the patient, as a result of findings of a larger or smaller tumor size in relation to breast volume, or due to comorbidity that may contraindicate a certain treatment. Any changes in the primary treatment plan after clinical examination must be clearly documented and motivated before CEM. (Additional file 5).

At the CEM examination, suspicious malignant findings will be noted according to a predefined protocol and if malignant-suspicious areas not previously located are identified by CEM they will be subjected to US-guided biopsy. The results of CEM will then be discussed at a second MDT conference, and taken into consideration in the primary treatment plan. (Additional file 8).

The whole study population will answer a short study-specific questionnaire including questions regarding possible allergy to iodinated contrast agent, weight and height, pre- or post menopausality, use of oral contraceptives, hormone replacement therapy or endocrine treatment after breast cancer, on-going pregnancy or breast-feeding, other diseases, previous surgery or radiotherapy to the breasts, and breast implants. This questionnaire will be administered at the appointment when the patient is informed about the study. Patients will also answer the preoperative version of the Breast-Q™ questionnaires [23]. These are globally used and validated patient-reported outcome measures. The Breast-Q™ questionnaires are currently the only validated, disease-specific questionnaires designed to evaluate different aspects of health-related quality of life and patient satisfaction related to breast cancer surgery.

The renal function of patients will be checked (normal range of serum creatinine 45–90 μmol/l) before the study inclusion, as the iodinated contrast agent may affect renal function.

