### Randomization

Web-based un-blinded simple randomization will be performed in *REDCap* by a randomization tool. Patients will be randomized 1:1 to either arm A, additional preoperative CEM or arm B, no further preoperative imaging. Randomization will be stratified between sites. All patients who fulfil the inclusion criteria will be registered in a screening log on-site.

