### Health-economic evaluation

Economic evaluation is a technique of identifying, measuring, valuing, and comparing the costs and consequences of two or more alternative programs or interventions [28]. Therefore, it is an analysis of costs and benefits (effects) between two or more alternatives. In the current study additional CEM will be compared to the current standard procedure i.e. only mammography and ultrasound. The perspective of analysis is important as it determines which costs and benefits should be included. The analysis will be performed from a healthcare perspective. The healthcare perspective is only concerned with costs burdening the healthcare sector, although the health benefits of the patients are the effectiveness measure.

The cost of the intervention and standard procedure for the control group can be calculated based on empirical data collected during the trial. The cost related to healthcare utilization will be obtained from the Skane register database. The effectiveness of trial will be measured as rate of reoperation and number of avoidable mastectomies. Furthermore, the patient-reported health-related quality of life at 1 year measured with the validated Breast-Q™ questionnaire will be used.

Irrespective of the measurement unit of the effectiveness, the results will be presented in terms of incremental cost-effectiveness ratios (ICERs) [28], which show the cost of an extra benefit for the intervention comparing to the control group. The results will be presented in a cost-effectiveness plane where the effectiveness and costs measures will be included as a distribution. The distribution will be obtained from individual level cost and effects data and the confidence interval will be obtained from bootstrapping [29]. In sensitivity analysis, a cost-effectiveness acceptability curve will be presented with a well-accepted willingness-to-pay value in Swedish circumstances [30].

The following broad cost and benefit categories will be included in the evaluation:

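### The one between-group test named, unadjusted Fisher's exact, ignores the site strata and leaves the preoperative Breast-Q unused; better-fitting analyses of the secondary endpoints cost nothing extra

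*Protocol article*

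**What the plan says.** All places are in the protocol article.

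- **Statistical analyses** gives one test for differences: Fisher's "exact test will be used to identify differences between groups and subgroups when applicable". No covariate or stratum is attached to it. The other inferential methods there, Pearson correlation and Bland-Altman, address a different question: these "statistics will be used for each modality regarding preoperative size estimation of the malignant changes compared with histopathological examination". They compare an imaging method with pathology, not arm with arm.
- **Randomization**: "Randomization will be stratified between sites". Patient enrollment names three centers.
- **Secondary endpoints** asks: "Is there a difference in health-related quality of life between patients that have undergone preoperative CEM and those who have not"? It also asks whether age, menopausal status, density, cancer type and microcalcifications influence plan change and size estimation.
- **Pre- and postoperative assessment and data collection**: "Patients will also answer the preoperative version of the Breast-Q™ questionnaires". Monitoring and follow-up adds the postoperative version at 1 year.
- **Health-economic evaluation** makes a second between-arm use of the questionnaire: "the patient-reported health-related quality of life at 1 year measured with the validated Breast-Q™ questionnaire will be used" as an effectiveness measure, and "the confidence interval will be obtained from bootstrapping".

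**The concern.** The Study design section says that the primary question could have been answered in a cohort and that most secondary endpoints are the reason for a control group. The analysis of those endpoints should therefore use what the design provides. Two things go unused in the stated method: the site strata and the preoperative Breast-Q. Fisher's test also takes only categorical data, so it does not fit a numeric score, an effect modifier such as age unless age is grouped, or a numeric size error.

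What is at stake is precision on secondary endpoints, and the risk that grouping of age is settled only once data are in hand. Bias and false-positive rates are not at issue.

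**Working it through.** **1. Does this touch the sample size?** Inputs from Power calculation: 18% against a null of 10%, 90% power, two-sided 5%.

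- One-sample formula: n = [(1.960 × √(0.10 × 0.90) + 1.282 × √(0.18 × 0.82)) / 0.08]² = 182.4.
- With continuity correction: (n/4) × (1 + √(1 + 2/(n × 0.08)))² = 194.7, that is 195, the article's figure.
- Dropout: 195/0.90 = 217, consistent with 220 recruited.
- A two-sample comparison of 10% with 18% would need 394 per arm.

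So 195 is a one-sample figure for the CEM arm against 10%. Choices about between-arm tests do not enter it.

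**2. Binary endpoints and site.** Simulation with no true arm effect: 195 per arm, three equal sites with exactly 65 per arm in each, 20,000 trials per row, two-sided 5%. The site event rates are assumptions; the documents give none.

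| Site event rates | Fisher, pooled | Cochran-Mantel-Haenszel by site |
|---|---|---|
| 15 / 15 / 15% | 3.6% | 5.0% |
| 8 / 15 / 22% | 3.2% | 4.7% |
| 5 / 15 / 30% | 2.8% | 5.1% |

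Simulation error is about √(0.05 × 0.95/20,000) = 0.15 percentage points. The first row shows that most of the gap arises even when sites do not differ, because Fisher's test is discrete and conditional. Ignoring site accounts for the further fall from 3.6% to 2.8%. That part depends on arms being balanced within site. The article calls the randomization simple as well as stratified; if allocation within site is unrestricted, the further fall should largely disappear, while the first-row gap remains.

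**3. Breast-Q and its baseline.** With correlation ρ between the preoperative and 1-year scores, ANCOVA multiplies the variance of the arm difference by 1 − ρ², relative to an unadjusted comparison of means. The detectable difference at 80% power and 195 per arm, in SD units, is (1.960 + 0.842) × √(2/195) × √(1 − ρ²).

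| ρ (assumed) | Variance factor | Detectable difference | Unadjusted n per arm for the same precision |
|---|---|---|---|
| 0 | 1.00 | 0.284 SD | 195 |
| 0.3 | 0.91 | 0.271 SD | 195/0.91 = 214 |
| 0.5 | 0.75 | 0.246 SD | 195/0.75 = 260 |
| 0.7 | 0.51 | 0.203 SD | 195/0.51 = 382 |

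The comparator here is an unadjusted comparison of means, not Fisher's test.

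**4. Effect modifiers.** Expected plan changes in the CEM arm: 0.18 × 195 = 35. One term each for age, density, menopausal status, microcalcifications and mode of detection, plus two for cancer type (ductal, lobular, other), makes seven parameters, or 35/7 = 5 events per parameter. That is thin for a joint model, so any regression must be small.

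**The case against.** The strongest reply is that the article confines Fisher's test to cases where it is applicable, and that a condensed article may leave the model for a patient-reported score to an analysis plan not shown here. This stands in part. A reader might infer that Breast-Q will be dichotomised, its baseline discarded or age split at the median. The text commits to none of these, so the information lost by such a split is not counted here. Nor does it say that no other method will be used.

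Four further replies also stand:

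- BI-RADS density is already categorical, as are most of the other listed modifiers. The grouping problem concerns age and software-calculated density.
- Fisher's test is valid for reoperation, avoidable mastectomy and recurrence. A stratified test is a gain in efficiency, not the repair of an invalid analysis.
- The economic evaluation already compares 1-year Breast-Q between arms with bootstrap intervals. It is estimation for cost-effectiveness, with no baseline or site adjustment stated.
- The baseline-adjustment gain applies to quality of life. To say that power is lost on most secondary endpoints would be too broad.

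The replies do not remove the core. A test is named for differences between groups, it takes no account of a stratification factor that the article itself fixes, and a baseline measurement is collected for which no between-arm use is stated.

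**Conclusion.** The concern holds in a limited form. As stated, the between-group method is valid for the binary secondary endpoints but conservative: 2.8 to 3.6% actual error at a nominal 5%, under assumed site rates and exact balance within site, and mostly because of the test itself rather than the omission of site. For Breast-Q it is the wrong kind of test for a numeric score, and a variance reduction of 9 to 49% is available for an assumed correlation of 0.3 to 0.7. That gain also assumes that some scales appear in both questionnaire versions, and that the preoperative form is completed before allocation is known; the documents settle neither.

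The consequence is lost precision on secondary endpoints. The primary comparison, the 195 evaluable patients and the 440 recruited are untouched. The change is worth making, but no conclusion of the trial would be invalid without it.

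**What to change.** State the following in the analysis plan before the data are analysed, or confirm that it is already there:

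1. **Reoperation, avoidable mastectomy, recurrence or new cancer:** compare arms with site as stratum, using a Cochran-Mantel-Haenszel test and a Mantel-Haenszel risk difference with confidence interval.
2. **Breast-Q at 1 year:** ANCOVA on arm, preoperative score and site, for each scale that appears in both versions. Specify that the baseline form is completed before randomization.
3. **Effect modifiers, CEM arm only, labelled exploratory:** logistic regression of plan change with age kept continuous and few covariates, given about 35 expected events; regression of size error on the listed factors.

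The cost is wording. Site, both questionnaires, age, density, pathology and size measurements are already collected, and no extra patients or visits are needed.

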A study-specific predefined imaging reporting protocol will be used for all imaging methods (DM, US and CEM), to assess morphological changes (solid tumors and/or micro calcifications), location of the lesions, size of each lesion and total extent of the malignant area (Additional files 1, 2, 6 and 7). The estimates of size will then be compared with the results from histopathological examination, which is considered to be the reference standard. Mammographic breast density will be evaluated according to the classification of American College of Radiation, Breast Imaging Reporting and Data System, 5th Edition (ACR BI-RADS) [24]. Background parenchymal enhancement on CEM will be classified as minimal, mild, moderate and marked. Findings will be classified as mass/lesion (visible on at least two views) or non-mass enhancement in as focal, linear, segmental regional, multiple regions, diffuse. Visual assessment of level of CEM enhancement in lesion/area will be reported as mild, moderate or marked. Classification of background parenchymal enhancement, findings and level of enhancement are described for MRI in ACR BI-RADS 5th edition [24], and will in this study be adapted for CEM, as suggested by Lobbes et al. [25]. Breast volume will be calculated from mammography images from measurements of width, *w*, and height, *h*, from the cranio-caudal projection of the mammogram, together with the compression, *c* (thickness of the breast when compressed during mammography), defining the breast as a half-elliptical cylinder, using the equation: $$ volume\ \left({cm}^3\right)=\raisebox{1ex}{$\pi $}\!\left/ \!\raisebox{-1ex}{$4$}\right.\times whc $$
*(cm)* [26, 27]. (Additional file 4). A software will also be used to calculate breast density and volume, for example Libra or Volpara™.

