Information will be obtained from the histopathological report on the total tumor extent, the size of each tumor if multiple tumors, the type of cancer (ductal, lobular, other), uni−/multifocality, ductal carcinoma in situ (DCIS) / pleomorphic lobular carcinoma in situ (LCIS), histological grade, biomarkers: estrogen receptor, progesterone receptor, Her-2 status and Ki67. The total tumor extent will be given including and excluding classic LCIS (LCIS-C) when present. LCIS-C does not affect treatment and is usually not visible at imaging. Data on adverse events related to CEM, e.g. the use of the iodinated contrast agent, will be collected directly after the examination and recorded. (Additional file 9).

The CEM examinations will be performed using a Senographe Pristina™ mammography system equipped with the software SenoBright™ HD for CEM (*GE Healthcare*). The CEM images will be read by at least two experienced radiologists in consensus, and with access to the images and results of routine clinical imaging. If additional tumors are found compared to the initial routine clinical imaging, a second-look US examination will be performed.

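### The size-accuracy question compares CEM with mammography and ultrasound, but the stated analysis describes each modality separately and includes Pearson's r, which does not measure accuracy

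*Protocol article*

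**What the plan says.** The protocol article, Secondary endpoints, asks: "Does preoperative CEM show better accuracy in tumor size estimation than mammography and ultrasound, in comparison with histopathological examination". Histopathology is the benchmark (Pre- and postoperative assessment and data collection): "The estimates of size will then be compared with the results from histopathological examination, which is considered to be the reference standard".

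For the analysis, Statistical analyses states that Pearson's correlation coefficient and Bland–Altman "statistics will be used for each modality regarding preoperative size estimation of the malignant changes compared with histopathological examination". It adds: "Mean and median values of the largest individual lesion and the total extent will be presented". It also plans a restricted analysis: "A separate analysis will be carried out for an extent maximum of 5 cm due to the limitations in assessment by US". The only comparative test in that section is Fisher's: "exact test will be used to identify differences between groups and subgroups when applicable".

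Under Randomization, only arm A receives CEM. Patients in arm B have mammography and ultrasound but no CEM.

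**The concern.** The question sets one modality against two others, while the stated method sets each modality against histopathology and stops there. The section states no contrast between modalities and no interval for a difference in error. Fisher's exact test does not fill the gap: it is for categorical data in separate groups, whereas size errors are continuous and several come from the same patient.

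The choice of Pearson's r adds to this. The Background section reports that mammography and ultrasound both tend to read tumours too small. A constant or proportional shortfall of that kind leaves r unchanged, so r is silent on the error of most interest here.

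At stake is how firmly the trial can answer a named secondary question. Three sets of figures side by side invite a verdict on which is better, without an estimate of the difference or its uncertainty.

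**Working it through.** **Planning figure.** No sample size is stated for the size-accuracy question, and none is disputed. The only stated number is 195 per arm for the primary endpoint (Power calculation). It reproduces as a one-sample test of 18% against 10%, two-sided 5%, power 90%:

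- n = [(1.96·√(0.10·0.90) + 1.2816·√(0.18·0.82)) / 0.08]² = 182.4
- with continuity correction: (182.4/4)·[1 + √(1 + 2/(182.4·0.08))]² = 194.7, so 195

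It serves below only as a plausible number of arm A patients with complete data.

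**Inputs** (Results of the feasibility study; modality minus histopathology, unit not stated, 47 patients):

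- CEM: mean −1.36, SD 18.45
- mammography: mean −4.18, SD 26.20
- ultrasound: mean −8.36, SD 24.30

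**Step 1: what Bland–Altman gives.** Limits are mean ± 1.96·SD. Root mean squared error is √(mean² + SD²). The 95% CI for bias at n = 195 is mean ± 1.972·SD/√195.

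| Modality | Limits of agreement | Root mean squared error | Bias CI, n = 195 |
|---|---|---|---|
| CEM | −37.5 to 34.8 | 18.5 | −3.97 to 1.25 |
| Mammography | −55.5 to 47.2 | 26.5 | −7.88 to −0.48 |
| Ultrasound | −56.0 to 39.3 | 25.7 | −11.79 to −4.93 |

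This is informative. The CEM and ultrasound bias intervals do not overlap. The CEM and mammography intervals do, so for that pair the separate summaries leave the difference in bias open.

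**Step 2: what the paired contrast adds.** The SD of the within-patient difference in error is √(s₁² + s₂² − 2ρ·s₁·s₂). The correlation ρ between the two modalities' errors is not given, so it is assumed to lie between 0 and 0.9. For CEM against mammography the difference in bias is −1.36 − (−4.18) = 2.82, with s₁² + s₂² = 340.40 + 686.44 = 1026.84. At n = 195:

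| Assumed ρ | SD of difference | Standard error | 95% half-width | p |
|---|---|---|---|---|
| 0 | 32.04 | 2.29 | 4.53 | 0.22 |
| 0.5 | 23.31 | 1.67 | 3.29 | 0.093 |
| 0.7 | 18.71 | 1.34 | 2.64 | 0.037 |
| 0.9 | 12.52 | 0.90 | 1.77 | 0.002 |

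The same means and SDs therefore support opposite readings, depending on a quantity that per-modality summaries do not show.

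For CEM against ultrasound the difference in bias is 7.00. The half-width runs from 4.31 (ρ = 0) to 1.57 (ρ = 0.9), and p is 0.0016 or less throughout.

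**Step 3: spread.** The Pitman–Morgan test compares paired SDs through r* = (s₂² − s₁²)/√[(s₁² + s₂²)² − 4ρ²s₁²s₂²] and t = r*·√[(n − 2)/(1 − r*²)]. For mammography at ρ = 0 and n = 195, r* = 346.04/1026.84 = 0.337 and t = 4.97, giving p = 1.5×10⁻⁶; p is smaller at larger ρ. Against ultrasound, p is 0.00015 or less. A difference in spread this large is clear whatever ρ is.

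**Step 4: Pearson's r.** For any constant a and any b > 0, corr(X, a + bY) = corr(X, Y). Adding 8.36 to every ultrasound reading would remove its whole mean error and lower its root mean squared error from 25.7 to 24.3, yet r would not move. The same holds if every reading is multiplied by a fixed fraction. This is algebra and needs no assumption about tumour sizes.

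**The case against.** The strongest reply is that Bland–Altman is an agreement method and already reports bias and spread. Step 1 shows that side-by-side figures can be clear, as for ultrasound bias, and Step 3 shows the same for spread. This stands. A reader might infer that the endpoint cannot be answered at all; the documents do not support that. Nor do they support the inference that CEM could be called better because its r is larger. The article sets no such criterion, and its feasibility results on this question are given as Bland–Altman means and SDs, with no r.

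A second reply is that the analysis set and a paired test are commonly left to an analysis plan, which is not shown here. This stands in part: such a plan may already contain the comparison. But the article does name methods for this question. Those methods do not match the question, and one of them does not measure accuracy.

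Two further inferences should be resisted. First, a reader might suppose that arm B mammography and ultrasound sizes will be pooled with those of arm A. The article does not say so; it simply does not name the patients for this analysis. Second, CEM is read "with access to the images and results of routine clinical imaging". One might conclude that the comparison is invalid, but this is openly stated and fits the declared aim of assessing CEM's added value. It is a matter of reading design, separate from the choice of statistic.

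**Conclusion.** The point holds as a mismatch between a comparative secondary question and a per-modality analysis, together with a correlation coefficient that cannot serve as evidence of accuracy. The planned Bland–Altman analysis is valid description; what is not stated is an estimate of the difference between modalities.

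Its size is shown by CEM against mammography: a bias difference of 2.82 at n = 195 with p anywhere from 0.22 to 0.002. Differences as large as the ultrasound bias or the mammography SD would be evident either way.

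These figures assume that the trial reproduces the feasibility means and SDs, that errors are roughly normal, that ρ lies between 0 and 0.9, and that 195 arm A patients have all the measurements. They concern bias and SD. The documents do not give what is needed to compute power for a comparison of absolute errors, so none is claimed. The statement about r depends on none of these assumptions.

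**What to change.** State the following for the size-accuracy endpoint:

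- Population: arm A patients with a histopathological size and a recorded size for the modalities being compared.
- Estimate: the paired within-patient difference in absolute error against histopathology, for CEM versus mammography and for CEM versus ultrasound, each with a 95% CI. The Wilcoxon signed-rank method with its interval, or a mixed model with a patient effect, would both serve.
- Scope: total extent, and the already planned analysis up to 5 cm.
- Description: per-modality Bland–Altman bias and limits, calculated in the same patients.
- Pearson's r: descriptive only, not evidence of accuracy.

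The cost is a few lines of text and a little extra analysis. No new data are needed, because these sizes are already to be recorded.
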